Prognostication of motor outcome following neonatal stroke has been an active area of research. Magnetic resonance imaging (MRI) assessment of the posterior limb of the internal capsule (PLIC) has been shown to correlate with the development of hemiparesis (11, 12). Quantitative scoring systems such as the Modified Pediatric ASPECTS have also been developed to correlate infarct volume with clinical outcomes (13). Additionally, the Hammersmith Infant Neurological Examination (HINE) and general movements evaluation are validated tools for early prediction of cerebral palsy (12). We acknowledge that this registry enrols only diagnosed cases; therefore, cumulative incidence will be calculated using total live births from all 22 participating hospitals as the denominator. However, this represents a hospital-based cohort rather than true population-based surveillance, and referral patterns may bias incidence estimates.

Shenzhen is particularly suitable as a model region due to its annual birth rate of approximately 200,000 live births, >98% NICU coverage across all districts, universal availability of cranial MRI and video-EEG at all participating hospitals, and the fact that >95% of regional births occur within the 22 study hospitals.

Therefore, establishing a prospective, multicenter cohort and dedicated registry is an urgent and foundational step. Such a resource is essential for accurately defining the disease burden, identifying associations with prenatal and perinatal factors that may inform future interventional studies, and mapping the evolution of neurodevelopmental outcomes from infancy through early childhood. By capturing comprehensive, longitudinal data within a real-world clinical setting, a registry can bridge the critical evidence gap between isolated clinical observations and population-level understanding.

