### Study design

2.2

This multicenter, prospective, observational cohort study aims to investigate the long-term neurodevelopmental outcomes of neonates with stroke. The study is planned to run for six years, from January 2025 to December 2030, in Shenzhen, China. The initial network comprises 22 collaborating hospitals, with Shenzhen Children's Hospital as the lead institution and Shenzhen People's Hospital as the primary coordinating center.

The study aims to recruit 300 neonates diagnosed with neonatal stroke, following them prospectively for five years to assess their neurodevelopmental trajectory. Additional hospitals may be included throughout the study period. A detailed study flow diagram is presented in Figure 1.

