#### Inclusion criteria

2.3.1

Participants must meet all the following criteria:
Gestational age ≥28 weeks and ≤28 days postnatal, with identified stroke risk factors. (Extremely preterm infants <28 weeks are excluded by design due to diagnostic challenges and different pathophysiology.Clinical presentation of acute encephalopathy or seizures.Neuroimaging confirmation (MRI) of stroke (arterial ischemic, hemorrhagic, or cerebral venous sinus thrombosis), excluding other common etiologies. Clinically silent infarctions (incidental findings on imaging without clinical symptoms) will be excluded. To ensure complete case ascertainment, all neonates with identified risk factors for stroke (e.g., congenital heart disease, extracorporeal membrane oxygenation, or severe perinatal asphyxia) will undergo systematic screening with cranial MRI, and any asymptomatic infarctions detected will be documented separately but excluded from the primary analysis cohort**.**Parental or legal guardian consent.

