#### Primary outcomes

2.5.1

Registry-based incidence of neonatal strokes in Shenzhen.

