### Statistical analysis plan

2.7

All analyses will be performed using SPSS (Version 27.0) and R (Version 4.4.1).
Descriptive Statistics: Continuous data will be presented as means ± SD (for normally distributed data) or as medians [IQR] (for non-normally distributed data). Categorical data will be analyzed using Chi-square or Fisher's exact tests.Incidence and Survival Analysis: Registry-based incidence and survival rates will be stratified by gestational age, sex, birth weight, and hospital level.Predictive Model Development:
Predictor Selection: LASSO regression will be used to identify potential predictors.Model Building: Multivariable logistic regression will identify independent factors associated with poor neurodevelopmental outcomes.Model Validation: Internal validation using bootstrap resampling (1,000 repetitions) will assess model performance (discrimination, calibration, and clinical utility).A two-sided *p*-value < 0.05 will be considered statistically significant.

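### Infants born before 28 weeks cannot be cases but remain in the live-birth denominator, which understates incidence in any low gestational-age or birth-weight stratum that contains them

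*Protocol article*

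**What the plan says.** - **Primary outcome** (Protocol article, 2.5.1): "Registry-based incidence of neonatal strokes in Shenzhen".
- **Denominator** (Introduction): "cumulative incidence will be calculated using total live births from all 22 participating hospitals as the denominator". No gestational-age limit is attached here or elsewhere. The caveat that follows covers only the hospital basis of the cohort and referral patterns.
- **Numerator** (2.3.1 Inclusion criteria): the first criterion reads "Gestational age ≥28 weeks and ≤28 days postnatal, with identified stroke risk factors", and the protocol adds "Extremely preterm infants <28 weeks are excluded by design due to diagnostic challenges and different pathophysiology".
- **Breakdown** (2.7 Statistical analysis plan): "Registry-based incidence and survival rates will be stratified by gestational age, sex, birth weight, and hospital level". No cut-points are given.
- **Subtypes**: section 2.4.4 defines hemorrhagic stroke only for term infants of 37 to 42 weeks, while the Discussion plans subtype-specific analyses of all primary and secondary outcomes.

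**The concern.** A cumulative incidence needs a denominator made up of births that could have become cases. Here both parts are stated, and one group of births is in the denominator with its contribution to the numerator fixed at zero. This is a mismatch between two stated rules, not a detail left to a fuller document.

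The stake is mainly in the breakdown. Births below 28 weeks are concentrated in the lowest gestational-age and birth-weight bands. A term band contains none of them, so its rate is unaffected. A comparison of the lowest band with term infants would therefore carry the whole bias, and part of the reported contrast would come from the denominator rather than from the disease. A separate band below 28 weeks would show zero incidence by construction, which a reader could take for absence of stroke.

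**Working it through.** **Inputs from the document.** Births in the region: "annual birth rate of approximately 200,000 live births". Coverage: ">95% of regional births occur within the 22 study hospitals". Duration: "The study is planned to run for six years, from January 2025 to December 2030, in Shenzhen, China". Planned cases: 300 (2.2 Study design). The protocol states no expected incidence for the registry, no share of births below 28 weeks and no stratum limits, so there is no figure of its own on this point to reproduce.

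**Assumptions, not in the document.** Births below 28 weeks are e = 0.2-0.6% of live births, and births at 28-31 weeks are v = 0.6-1.0%. The band below 32 weeks is hypothetical.

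**Step 1. General form.** Let a stratum have N live births, a fraction f of them below 28 weeks, and C cases, all from the other births.

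- Reported incidence = C / N
- Incidence among eligible births = C / [(1 − f) N]
- Ratio = 1 − f, so the relative understatement is exactly f, and the correction factor is 1 / (1 − f)

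**Step 2. Overall incidence.** Births covered: 200,000 × 0.95 × 6 = 1,140,000. With 300 cases this is 1 in 1,140,000 / 300 = 1 in 3,800.

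- f = 0.2%: 3,800 × 0.998 gives 1 in 3,792
- f = 0.6%: 3,800 × 0.994 gives 1 in 3,777

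For comparison, the Poisson 95% margin on 300 cases is about 1.96 / √300 = ±11%.

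**Step 3. Gestational-age strata.** For a band below 32 weeks, f = e / (e + v).

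| Lowest band | e | v | f = understatement | Correction factor |
|---|---|---|---|---|
| starts at 28 weeks | n/a | n/a | 0% | 1.00 |
| below 32 weeks | 0.2% | 1.0% | 0.2 / 1.2 = 17% | 1.20 |
| below 32 weeks | 0.4% | 0.8% | 0.4 / 1.2 = 33% | 1.50 |
| below 32 weeks | 0.6% | 0.6% | 0.6 / 1.2 = 50% | 2.00 |
| separate band below 28 weeks | n/a | n/a | 100% | undefined (incidence 0) |

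Broader bands are affected less: with f = 5% the factor is 1.05.

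**Step 4. Birth-weight strata.** The same identity holds, with f the share of births below 28 weeks in the weight band. Starting the gestational bands at 28 weeks does not help here, because a low-weight band takes in births by weight whatever their gestation. Only a restriction on the denominator itself brings f to zero.

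**Step 5. Hemorrhagic subtype.** If the definition in 2.4.4 is applied literally, no birth outside 37-42 weeks can be a hemorrhagic case. For that subtype the ineligible share is then every birth outside that range, and a limit at 28 weeks would not remove the mismatch.

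**The case against.** The strongest reply has four parts.

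1. **The primary rate hardly moves.** This stands. A bias of 0.2-0.6% is small beside a sampling margin of about ±11%. A reader might infer that the headline incidence is materially wrong, but on these shares it is not.

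2. **The 17-50% is not a property of the plan.** This also stands. It needs birth shares and a band below 32 weeks that the document does not give. The upper end requires as many births below 28 weeks as at 28-31 weeks. Because 28 weeks is the entry floor, a lowest band starting there is a natural reading, and its bias is zero. A reader might take the range as a finding about this registry, but it is only an illustration. The reply does not rescue the birth-weight strata.

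3. **The lowest stratum will be sparse.** With an assumed 0.8% of births at 28-31 weeks and the overall rate of 1 in 3,800, one expects 1,140,000 × 0.008 / 3,800 = 2.4 cases. Sampling error could therefore rival or exceed the bias. That limits the practical effect, but it does not excuse a known bias in one direction that no amount of data removes.

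4. **Stratum counts may well be planned.** A reader might infer that a denominator described as a total cannot supply rates by gestational age, sex, birth weight or hospital level. The document does not support that. The wording names the source population and does not rule out counts by stratum. The promise of stratified incidence presupposes such counts, and an article can leave their tabulation to the full protocol. This is not part of the point.

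**Conclusion.** The mismatch is real and rests on the text alone: infants below 28 weeks are barred from the numerator, counted in the denominator, and nothing reconciles the two. The direction is downward and the size in any stratum is exactly f.

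The consequence for the overall primary incidence is under 1% on the assumed shares. For the promised strata the size depends on cut-points that the article does not set, anywhere from 0% to 100% by gestational age. Whatever those cut-points are, the lowest birth-weight bands are understated by an amount that cannot be computed from the document. The point deserves correction because it touches the breakdown of the primary outcome and costs little to repair, not because the headline figure is in danger.

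**What to change.** - In the Introduction and section 2.7, define the incidence denominator as live births at 28 weeks' gestation or later in the 22 hospitals.
- State that the same limit applies within every stratum, including birth weight, sex and hospital level.
- Start the lowest gestational-age band at 28 weeks and label it so.
- Reconcile the hemorrhagic-stroke definition in 2.4.4 (37 to 42 weeks) with the entry criterion in 2.3.1 (28 weeks or later). Then restrict the denominator for hemorrhagic-stroke incidence to births that could meet whichever definition is kept.

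The cost is a few sentences, plus a request that each hospital supply its birth counts with the gestational-age limit applied, overall and by stratum. This assumes that hospital birth records hold gestational age and birth weight, which the stratification by these variables already requires. Neither recruitment nor the sample size changes.

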#### Exclusion criteria

2.3.2

Participants will be excluded for any of the following:
Congenital structural brain malformations.Seizures attributable to a metabolic cause (e.g., electrolyte imbalances or hypoglycemia).Transfer to a non-participating center or voluntary discharge prior to enrollment.Refusal of informed consent by the parent or guardian.

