#### Recruitment, screening, and informed consent

2.4.1

Neonates meeting the inclusion criteria will be prospectively identified and recruited by trained neonatologists from the NICUs and pediatric wards of the 22 participating hospitals. Two attending neonatologists at each site will be responsible for patient enrollment using standardized diagnostic criteria.

Written informed consent will be obtained from the parents or legal guardians after a definitive diagnosis is made. The study adheres to the ethical principles of the Declaration of Helsinki and has received institutional ethics approval.

To ensure rigorous standardization across the 22 participating centres, all enrolling neonatologists will undergo a mandatory centralized training workshop focused on standardized case definitions, MRI interpretation using a validated study atlas, and EEG acquisition protocols. In parallel, to maintain longitudinal data quality, annual inter-rater reliability assessments will be conducted using 10 blinded test cases. For diagnostic adjudication, all stroke subtypes will be centrally reviewed by an expert committee comprising three senior neonatologists and two neuroradiologists at Shenzhen Children's Hospital, who remain blinded to the initial site-level diagnosis. Furthermore, neuroimaging will adhere to a harmonized 3T MRI protocol (including DWI, SWI, and MRA/MRV sequences). Where 3T MRI is not immediately available at a participating center, arrangements will be made for patient transfer to a center with 3T capacity, and this will be documented. Specific scoring approaches for infarct volume (modified Pediatric ASPECTS) and PLIC assessment will be used centrally. All video-EEG recordings will be centrally interpreted by a single epileptologist masked to all clinical and imaging data.

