#### Data elements and database modules

2.4.3

The online registry is divided into the following modules:
General and Hospital Information: Demographics, birth facility data, and administrative details.Family and Perinatal History: Family history, maternal/pregnancy data, labor/delivery details, and resuscitation history.Neonatal Clinical Presentation: Initial Status (e.g., blood glucose), seizure data, and comorbidities.Diagnostic Tests and Biological Samples: Coagulation tests, genetic data (optional), neuroimaging, and EEG results.Treatment and Discharge Summary: Details of therapies, discharge diagnosis, and treatment outcomes.Long-Term Follow-up Examinations: Data from 6m, 18m, 3y, and 5y visits, including Bayley-4C scores, EEG, MRI results, growth metrics, and epilepsy medication.Follow-up Conclusions: Final Status, including outcomes like epilepsy, cognitive impairment, motor disorders, and cerebral palsy, confirmed by pediatric neurologists and rehabilitation physicians.The complete data dictionary is available in Online Supplementary File 3.

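### The primary incidence counts cases by place of treatment but births by place of delivery, so outborn infants can enter the numerator without their births; restrict the primary numerator to infants born at the 22 hospitals

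*Protocol article*

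**What the plan says.** Section 2.5.1 names a single primary outcome: "Registry-based incidence of neonatal strokes in Shenzhen".

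- **Denominator.** The Introduction fixes it: "cumulative incidence will be calculated using total live births from all 22 participating hospitals as the denominator".
- **Cases.** Section 2.4.1 identifies them by where they are treated. They are "recruited by trained neonatologists from the NICUs and pediatric wards of the 22 participating hospitals".
- **Eligibility.** The first inclusion criterion in section 2.3.1 reads "Gestational age ≥28 weeks and ≤28 days postnatal, with identified stroke risk factors". The others concern clinical presentation, MRI confirmation and consent. Neither they nor the exclusions in section 2.3.2 mention place of birth or residence.
- **Losses before enrolment.** Section 2.3.2 excludes infants for "Transfer to a non-participating center or voluntary discharge prior to enrollment", and separately for refused consent.
- **Caveat.** The Introduction calls the cohort hospital-based and concedes that "referral patterns may bias incidence estimates". It gives no direction, size or correction.
- **Strata.** Section 2.7 stratifies incidence by gestational age, sex, birth weight and hospital level. It does not separate inborn from outborn infants.
- **Data already collected.** The first registry module in section 2.4.3 covers "Demographics, birth facility data, and administrative details".

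**The concern.** A cumulative incidence needs a numerator drawn from the births in its denominator. Here the two rules, as stated, describe different groups: infants treated at the 22 hospitals, and infants born there. The two groups differ by the infants referred in and the infants lost from the network. Each infant born elsewhere and enrolled adds one case and no birth.

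The rate is to be reported for Shenzhen. The Introduction sets out earlier Chinese rates of 1 in 2,660 and 1 in 8,373 and attributes the difference partly to referral to tertiary centres. A new rate that carries the same referral artefact is harder to compare with either. The hospital-level stratum is the most exposed. If cases are assigned to the hospital that treats them, a referral centre collects cases from births counted at other network hospitals, or counted nowhere. Section 2.4.1 itself provides for transfer to a centre with 3T MRI, so the birth hospital and the diagnosing hospital can differ even within the network.

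**Working it through.** **The plan's own figures.** The protocol states no target incidence and no precision for the primary outcome, so there is no incidence figure to reproduce. Its one computed design figure, the evaluable sample in section 2.6, does reproduce: 300 × (1 − 0.10 − 0.20) = 210. It does not bear on this point.

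**Inputs from the protocol.** About 200,000 live births a year in Shenzhen; more than 95% of regional births in the 22 hospitals; six years (January 2025 to December 2030); 300 planned cases.

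**Assumed.** The outborn share of cases f, and the share m of inborn cases that are missed. The protocol gives neither.

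**Step 1: illustrative crude rate.** Denominator = 200,000 × 0.95 × 6 = 1,140,000 births. If 300 cases are enrolled, the crude rate is 300/1,140,000, or 1 in 3,800.

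**Step 2: effect of outborn cases alone.** If a share f of enrolled cases is outborn, the crude rate is 1/(1 − f) times the inborn rate, a relative excess of f/(1 − f).

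| Assumed f | Inborn cases of 300 | Inborn rate | Excess of crude rate |
|---|---|---|---|
| 5% | 285 | 1 in 4,000 | +5.3% |
| 10% | 270 | 1 in 4,222 | +11.1% |
| 20% | 240 | 1 in 4,750 | +25.0% |
| 30% | 210 | 1 in 5,429 | +42.9% |

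**Step 3: what the protocol bounds.** At most 5% of regional births fall outside the network. At equal risk, and with every such case referred in, the in-city excess is at most 0.05/0.95 = 5.3%. No figure bounds referrals from outside Shenzhen.

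**Step 4: comparison with sampling error.** The exact Poisson 95% interval on 300 cases runs from 267.0 to 335.9, which is −11% to +12%. The in-city part is about half of that. A share f of roughly 10% would match it.

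**Step 5: interval coverage.** Suppose the true inborn count is 380 (1,140,000/3,000) or 228 (1,140,000/5,000), all inborn cases are found, and the observed count is Poisson with mean 380/(1 − f) or 228/(1 − f). The exact 95% interval then covers the true inborn rate as follows.

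| Assumed f | True rate 1 in 3,000 | True rate 1 in 5,000 |
|---|---|---|
| 5% | 83% | 88% |
| 10% | 45% | 63% |
| 20% | 0.5% | 6% |

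Only the 5% row corresponds to a figure in the protocol. The other rows are hypothetical.

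**Step 6: losses in the other direction.** If a share m of true inborn cases is not enrolled but their births are counted, the ratio of estimated to true rate is (1 − m)/(1 − f).

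- f = 5%, m = 10%: 0.90/0.95 = 0.95
- f = 10%, m = 10%: 0.90/0.90 = 1.00
- f = 20%, m = 10%: 0.90/0.80 = 1.125

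The net error can therefore take either sign.

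**The case against.** **The numerator is inferred.** The protocol fixes the denominator but nowhere says that every enrolled case, inborn or not, is counted. The article is condensed, a separate analysis plan may restrict the numerator, and recording birth facility fits such a rule. This stands in part: the restriction may exist elsewhere. But the recruitment rule and the denominator are both stated here, and applied as written they give a mismatched ratio for the primary outcome.

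**The bias is disclosed.** It is, in general terms, and the outcome is labelled registry-based throughout. Non-disclosure is therefore not the complaint. The caveat corrects nothing, although this component can be removed with data already collected.

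**The documented size is small.** This stands. About 5% is all that the protocol's figures support.

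**The restriction could move the estimate away from the truth.** With f = m = 10%, the two errors cancel, and restricting to inborn cases alone would take the ratio from 1.00 to 0.90. This is arithmetically right, but the cancellation is chance. After the restriction, the remaining error from lost inborn cases has a known direction, undercount, and can be partly measured.

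A reader might infer two stronger conclusions. The first is that the reported incidence will be too high. The documents do not support that, because transfers out, voluntary discharge and refused consent remove inborn cases whose births may stay in the denominator. The second is that the registry could not help resolve the earlier discrepancy. That does not follow either: 8,373/2,660 is 3.15-fold, and outborn cases alone would need f = 1 − 2,660/8,373 = 68% to span it. The Introduction also names case ascertainment and imaging as causes.

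**Conclusion.** The concern holds as a mismatch between numerator and denominator in the primary outcome. Taken alone, the outborn component can only push the rate up, by f/(1 − f). The in-city part is at most about +5%, given the stated coverage, equal risk and complete referral. Anything larger depends on referrals from outside Shenzhen, which the eligibility criteria do not exclude and the protocol does not quantify; +11% and +25% are what an assumed f of 10% and 20% would give. The direction of the net error in the final rate is not determined. The change is worth making before analysis because it affects the primary outcome, removes this component completely and needs no new data.

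**What to change.** In sections 2.5.1 and 2.7:

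- Define the primary numerator as cases born at one of the 22 hospitals, identified from the recorded birth facility.
- Count each case once, under its birth hospital, whichever site diagnoses or treats it. Apply the same assignment in the hospital-level stratum.
- Report outborn cases as a separate count, and show the all-cases rate as a sensitivity analysis.
- Keep outborn cases in the follow-up cohort and the prediction model.
- Report the number of known eligible inborn infants not enrolled (transferred out, discharged or consent refused), so that the remaining bias is identified as undercount.

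The cost is a few sentences, a filter on an existing field and a tally of known non-enrolled infants. Recruitment and the planned sample size do not change. The downside is a slightly smaller headline case count, and so a slightly wider interval for the primary rate.
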